### Secondary outcomes

The secondary outcomes were eating behaviours, which was considered an index of behavioural change and is often held up as the goal of nutrition education. Three eating behaviours (per week) were considered: mealtime balance, or eating ‘balanced meals comprising a staple food, a main dish, and a side dish’ [37], ‘eating dark green vegetables’, and ‘eating full servings of vegetables (5 small dishes or approx. 350 g per diem)’ [38]. The mealtime balance behaviour has been shown to facilitate nutrient intake and improve nutritional status [39–41]. To explain the staple foods, main dishes, side dishes, and vegetable servings, we posted sample photographs for reference in terms of size and amount, and stipulated that respondents should always check these photographs before responding. Because daily eating behaviours (two items) were checked using these photographs depicting single (70 g) servings of vegetables, participants were also asked to answer how many vegetable servings they consumed per diem. This item reflects the fact that, as demonstrated by Ozawa et al. [42], the behavioural goal of ‘five or six small [vegetable] dishes a day’ can potentially serve as an easily grasped indicator of consuming 350 g per diem. Additionally, the amount of vegetables eaten each day (in g) was also self-reported.

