### Assessment

The primary outcome variable was assessed using a self-administered questionnaire in Japanese. Regarding the assessment, at baseline (T1), primary outcomes, transtheoretical model [31], self-efficacy [32], dietary knowledge [33], perceptions of neighborhood food environments within secondary outcomes, and all other measurements. After completion of the 5-week intervention, participants received an e-mailed request to participate in the post-intervention survey (T2). At post-intervention survey (T2), we assessed the all primary outcomes, all secondary outcomes, all other measurements excluding the subjective economic status. We evaluated about the participants’ satisfaction of process evaluation as after intervention. Finally, participants received another e-mail request to participate in a follow-up survey 3 months after completing the intervention (T3). At follow-up survey (T3), we assessed the all primary outcomes, all secondary outcomes, and all other measurements excluding the subjective economic status.

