### Sample size

The sample size was calculated using G*Power [50]. We set an effect size of 0.5, an α of 0.05, and a power of 0.95. With the expectation that two-thirds of participants would drop out, the size of the intervention group was set at 900 subjects, while that of the control group was set at 600 subjects with the expectation that a half of participants would drop out. Furthermore, we aimed to divide the intervention and control groups further according to income (low and high).

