### Statistical analyses

All statistical analyses will be performed with IBM SPSS Statistics 21.0. For continuous variables, independent t-tests will be used to determine inter-group differences and Man–Whitney U-tests for intra-group comparison, while the χ^2^ or an equivalent test is to be used to determine the associations between categorical variables. Because this is a prospective RCT involving repeated measures, repeated measures analyses of variance will be applied to determine significant differences within the study groups. We also considered the possible effect of time on groups. The evaluation of the intervention is based on an intention-to-treat analysis. A *p*-value of 0.05 has been set as the level of significance.

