## Discussion

This study describes an RCT of a web-based nutrition education programme. Promoting vegetable intake is an important challenge for health promotion during adulthood, regardless of socio-economic status. Japanese adults of all household income levels consume less than approximately two-thirds of the recommended daily amount (i.e. 350 g or five servings per day). Support for the increased intake of appropriate vegetables seems best implemented using a population-based approach, as this issue is necessary for not only lower-income groups, but also the entire adult population. Web-based nutrition education programmes are communication tools that use ICT, in particular the Internet. In other words, it is a health education tool for which future expansion can be anticipated in fields of health promotion. If we could show that such web-based nutrition education programmes are beneficial for improving vegetable intake, our population-based approach would enable lower-income groups to catch up in terms of averaged daily intake of vegetables while also contributing to the resolution of the overall deficiency in vegetable intake in Japan’s overall adult population. So far as we know, this is the first report regarding a web-based nutrition education programme developed with a focus on socio-economic status.

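### Vegetable intake carries the trial's main claim, but it is the main outcome in the Abstract, secondary in the Methods, and measured in four ways at two visits with neither the measure nor the visit fixed

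*Protocol article*

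**What the plan says.** - **Objective and hypothesis.** The end of the Background sets the main objective as verifying a 5-week programme that promotes vegetable intake. The Background and the Intervention programme section both hypothesise a gain of about 70 g, or one serving, a day. The action goal in the Intervention programme section is five servings, or one more serving, a day.
- **Abstract.** The main outcome is vegetable eating, described as 350 g a day or five small bowls.
- **Primary outcomes (Methods).** Diet-related quality of life and self-rated health. No vegetable measure is listed.
- **Secondary outcomes (Methods).** Besides mealtime balance there are four vegetable items. Two are weekly: dark green vegetables, and full servings (five small dishes or about 350 g). Two are daily: "participants were also asked to answer how many vegetable servings they consumed per diem", and "Additionally, the amount of vegetables eaten each day (in g) was also self-reported".
- **Assessment.** The secondary outcomes are collected at T2 and again later: "At follow-up survey (T3), we assessed the all primary outcomes, all secondary outcomes".
- **Statistical analyses.** Independent t-tests serve for differences between groups, with no time point given. Repeated measures ANOVA is also named, and the effect of time on groups is mentioned. "A *p*-value of 0.05 has been set as the level of significance".
- **Discussion.** The population-level conclusion depends on the vegetable result: "If we could show that such web-based nutrition education programmes are beneficial for improving vegetable intake".

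**The concern.** The statement the trial most wants to make is that the programme raises vegetable intake. The two primary outcomes in the Methods cannot support it, so it has to come from the secondary family, and the article does not say which member of that family decides.

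The four items can disagree. Someone who moves from two to three servings a day meets the one-more-serving goal, yet does not reach five a day. According to the Background, the five-serving habit is held by only about 10% even in higher-income groups, so that item could stay flat while mean servings rise. Dark green frequency could rise without any change in total servings.

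If the measure and visit are settled only after the results are seen, the headline depends on that choice, and 0.05 no longer describes the chance of a false claim.

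**Working it through.** **1. Can the text settle which measure decides?**

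- The Abstract's main outcome matches the full-servings item in content. However, 350 g or five bowls a day could be read from the weekly frequency, the daily serving count or the grams. No visit is named.
- The Primary outcomes section contradicts the Abstract by placing no vegetable item among the primaries.
- The Sample size section does not help. "We set an effect size of 0.5, an α of 0.05, and a power of 0.95" names no outcome.

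Neither the form nor the visit can be recovered from the article.

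**2. Inputs for the error rate**

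- Level per test: 0.05 (Statistical analyses). Sidedness is not stated, so two-sided is assumed, with critical value 1.96.
- Vegetable measures: 4 (Secondary outcomes).
- Visits after baseline: 2 (Assessment).
- Number of tests m: 4 if there is one test per measure (one fixed visit, or one repeated-measures test across visits); 4 × 2 = 8 if each visit is tested separately.
- Correlation ρ between test statistics: not given. Assumed common to all pairs and varied from 0 to 0.8.

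**3. Formulas, with no true effect on any measure**

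One named test gives 1 − 0.95 = 0.05, which reproduces the stated level. Its favourable half is 0.025.

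Independent tests:
- two-sided: 1 − 0.95^m, so 1 − 0.95^4 = 0.186 and 1 − 0.95^8 = 0.337
- favourable direction only: 1 − 0.975^m, so 1 − 0.975^4 = 0.096 and 1 − 0.975^8 = 0.183

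Correlated tests: write Z_j = √ρ·U + √(1−ρ)·e_j with U and e_j independent standard normal, and integrate over u with the standard normal density φ:
- two-sided: 1 − ∫ φ(u) [Φ((1.96 − √ρ u)/√(1−ρ)) − Φ((−1.96 − √ρ u)/√(1−ρ))]^m du
- favourable only: 1 − ∫ φ(u) [Φ((1.96 − √ρ u)/√(1−ρ))]^m du

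**4. Results: chance of at least one false positive**

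| ρ | m = 4, two-sided | m = 4, favourable | m = 8, two-sided | m = 8, favourable |
|---|---|---|---|---|
| 0 | 18.6% | 9.6% | 33.7% | 18.3% |
| 0.3 | 17.4% | 8.7% | 30.0% | 15.2% |
| 0.5 | 15.6% | 7.8% | 25.0% | 12.5% |
| 0.7 | 13.0% | 6.5% | 19.1% | 9.5% |
| 0.8 | 11.4% | 5.7% | 15.8% | 7.9% |

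With correlation 0.8 between measures and 0.7 between visits, simulation gives 18.3% two-sided for eight tests, inside the same range.

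**5. Ratios**

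- Two-sided against 0.05: 11.4/5 = 2.3 to 18.6/5 = 3.7 for four tests; 15.8/5 = 3.2 to 33.7/5 = 6.7 for eight.
- Favourable against 2.5%: 5.7/2.5 = 2.3 to 9.6/2.5 = 3.9 for four; 7.9/2.5 = 3.2 to 18.3/2.5 = 7.3 for eight.

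The four-test favourable column assumes a directional contrast. An omnibus group-by-time F test has no direction, so only the two-sided column would apply to it.

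**The case against.** **The Abstract does name a main outcome.** This stands in part. It would be wrong to say that the article names no vegetable outcome as deciding. But the Abstract fixes neither the form nor the visit, and the Methods contradict it.

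**Eight tests is a construction.** This stands. The Statistical analyses section names both t-tests and repeated measures ANOVA, so a separate test at each visit is one reading and not a stated rule. The four-test figures belong beside the eight-test ones. Counting dark green vegetables as a measure of intake is also a judgement, because it is a subtype of total vegetables.

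**No rule says that any one significant item proves the claim.** This stands. The Discussion sentence is conditional and is not an analysis rule. The error rates describe what the text permits, not what the authors said they would do.

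**Multiplicity among secondary outcomes belongs in an analysis plan.** This stands for the adjustment rule: one may exist that is not shown, and its absence here is no defect. It does not cover the choice of outcome that answers the main objective. That is a protocol matter, and the article states it inconsistently.

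**The weekly five-serving item does measure a stated goal.** This stands. Five servings is half of the action goal, so the item cannot be dismissed as irrelevant. It is insensitive only to the other half, one more serving.

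A reader might infer that a false claim of improvement is about five times as likely as stated. The article does not support that as a single figure. It needs eight separate tests and an assumed correlation of 0.5. For a one-directional claim it also needs 2.5% as the base: 12.5% is 2.5 times the stated 0.05.

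**Conclusion.** The concern holds as an inconsistency with a consequence. Vegetable intake is the subject of the main objective and the main outcome in the Abstract. In the Methods it is secondary, measured in four overlapping ways at two visits, with no deciding measure or visit.

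If any significant result could support the claim, the two-sided false-positive chance is about 11% to 19% for four tests and 16% to 34% for eight. Counting only results favouring the programme, it is about 6% to 10% and 8% to 18%, against 2.5% for one test. These figures rest on two-sided tests at 0.05, assumed correlations from 0.8 to 0, no true effect on any item, and no adjustment in a plan that is not shown. The exact multiple is uncertain, but every case examined exceeds the single-test rate. The unfixed deciding measure and visit do not depend on these assumptions.

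**What to change.** 1. Reconcile the Abstract with the Primary and Secondary outcomes sections, so that they agree on whether vegetable eating is the main outcome. Demoting the five-a-day and gram items without this step would deepen the conflict, because 350 g or five bowls is what the Abstract calls main.
2. In Secondary outcomes and Statistical analyses, name one vegetable measure and one visit, before outcome data by arm are seen, as the sole test for the statement that intake improved. One suitable choice is the between-arm difference in photo-referenced servings per day at T2, since a serving count captures both the one-more-serving and the five-serving goal in the Intervention programme section.
3. Test the same measure at T3 at 0.05 only if the T2 test is significant.
4. Report the other vegetable items as supportive, with estimates and 95% confidence intervals.
5. Tie the Discussion's conclusion on vegetable intake to the named test.

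The cost is a few sentences, with no new data or participants. The small downside is that a favourable result on a supportive item alone could no longer be claimed as proof of improved intake.

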### Other measurements

As our intention was to evaluate not only outcomes, but also the processes leading to behavioural change, we also employed secondary items assessing diet. We used a measure based on the transtheoretical model [31] (containing three items) to evaluate the intermediate factors relating to secondary-outcome eating behaviours, and a measure of self-efficacy [32] (also containing three items) as an evaluation of preparatory factors. We also used two items [33] to assess dietary knowledge concerning secondary-outcome eating behaviours. Perceptions of neighborhood food environments relating to eating behaviour was assessed with ten items [43, 44].

We also measured health literacy [45], which is defined as the knowledge, desire, and skills for acquiring, comprehending, evaluating, and making use of health information, using a scale with good validity for the Japanese population. In the context of our previous research, the relationship of health literacy with vegetable intake behaviour was shown to be unaffected by socio-economic status, whereas promotion of vegetable intake behaviour has the potential to improve health literacy [46]. In addition, we measured subjective economic status [47], household income [30], educational attainment [23, 24, 46], and other attributes (namely sex, age, marital status, living status, and employment status).

### Process evaluation

Adherence to the intervention was assessed by the number of log-ins and duration spent in the website. Furthermore, the participants’ satisfaction with the intervention was assessed by using a self-administered questionnaire at post-intervention. With reference to previous studies on programme development [48, 49], we also included an evaluation (5 items) of the nutrition education programme itself. The items were as follows: (1) was the content of the programme fun? (2) was the content of the programme easy to understand? (3) after participating, did you become aware of any problems in your own diet? (4) did you feel the programme was helpful as a health management material? and (5) as a health management material, did it make you want to participate again another time?

### Sample size

The sample size was calculated using G*Power [50]. We set an effect size of 0.5, an α of 0.05, and a power of 0.95. With the expectation that two-thirds of participants would drop out, the size of the intervention group was set at 900 subjects, while that of the control group was set at 600 subjects with the expectation that a half of participants would drop out. Furthermore, we aimed to divide the intervention and control groups further according to income (low and high).

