## Background

Appropriate vegetable intake appears to be effective for cancer prevention [1, 2] and is associated with reduced risks of cardiovascular disease [3, 4], obesity [5], and other lifestyle-related diseases. Health policy initiatives are promoting vegetable intake across all segments of the population worldwide. However, in practice, it has been widely reported that vegetable intake remains low among social disadvantaged groups in terms of household income and other indicators of socio-economic status [6, 7].

As part of efforts to promote vegetable intake among adults, several nutrition education programmes that have incorporated aspects of behavioural science theory have proven effective [8–10]. Web-based intervention programmes are of particular note, and several have been developed and verified outside of Japan [10–20]. Lauren et al. [17] compared the effects of face-to-face nutrition education with a web-based education, and found that changes in vegetable intake prompted by the web-based programmes were comparable with those achieved through the face-to-face programmes. Additionally, Bensley et al. [16] reported that provision of information through bulletins board increased vegetable intake by 0.2 serving while a web-based intervention increased intake by 0.6 serving.

Despite these promising findings, only the reports by Buller and Ball [13, 19] considered socio-economic status in relation to web-based nutrition education programmes, indicating an extreme paucity of research in this area. Buller et al. demonstrated that it is possible to implement web-based nutrition education programmes even in agricultural communities lacking an adequate web infrastructure. Of course, a remaining challenge is that their findings are limited to agricultural communities. There are no studies comparing the effects of different socioeconomic status.

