The RCT in this study is original in the following two regards. (1) It can verify the intervention effect for an adequate sample size, and (2) it can verify differences in the effect of a nutrition education programme by income strata. With this study, it will also be possible to verify the possible catch-up effect in relation to undesirable vegetable intake behaviour associated with low household income. Some reports have suggested that traditional classroom-based nutrition interventions might widen this disparity [6]. In contrast, with our study, it may be possible to show that a web-based nutrition education programme would inhibit the widening of this disparity.

Conversely, this study also has its limitations. It is possible that the results of the study will reflect the characteristics of individuals registered with the research company (e.g., tending to be young, high-earning, and highly educated [51–53]). To minimize this potential limitation, we have made sure to match participants with demographic distributions in terms of sex, age, and household income. In addition, we requested research cooperation from individuals whose household income data – which was our objective – had been recorded in advance. This helps to restrict attribute bias as well as negative response rates for delicate questions pertaining to household income and other matters. Second, during participant recruitment, we excluded individuals reporting household incomes of ten million JPY or more. This means that the results do not target the entire population. Accordingly, care must be taken when drawing general conclusions. However, a limit of less than ten million JPY still applies to 88.4% of the Japanese population. Finally, participants did not have contact with one another (either in person or through indirect communication) for the period of the intervention. For this reason, it is possible that rates of adherence to nutrition education programmes will be lower than they would with enforced participation.

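### The stated sample-size inputs (effect size 0.5, alpha 0.05, power 0.95) do not give 900 + 600, and the 0.5 is tied to no outcome; the trial has ample power for 0.5 overall, but about 86% for an income interaction of that size

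*Protocol article*

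**What the plan says.** The Sample size section of the protocol article gives the software ("The sample size was calculated using G*Power") and three inputs: "We set an effect size of 0.5, an α of 0.05, and a power of 0.95". It then moves straight to enrolment in the intervention arm: "With the expectation that two-thirds of participants would drop out, the size of the intervention group was set at 900 subjects". For controls it gives 600, on an assumed dropout of one half. The next sentence adds that the arms are to be subdivided into low and high income, with no number or power attached.

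The section does not give the number that the software returned, the test, the sidedness, or the outcome to which 0.5 refers. Statistical analyses supplies a candidate test: "For continuous variables, independent t-tests will be used to determine inter-group differences". It also says that a p-value of 0.05 "has been set as the level of significance", and that the evaluation is by intention to treat.

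The main outcome is described in two ways. The Abstract (Methods/Design) gives vegetable eating. The Primary outcomes section gives diet-related quality of life and self-rated health, and vegetable eating appears under Secondary outcomes.

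Strengths and limitations claims of the trial: "It can verify the intervention effect for an adequate sample size". It also claims that differences in effect between income strata can be verified. The Background makes the variation of effect with socio-economic status the secondary objective.

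**The concern.** The article publishes the inputs, the dropout rates and the result of one calculation, and these do not agree. Either a published input is wrong, or something that determined the size was left out. A fuller protocol could supply the missing step, but it could not make the three published inputs equal the published sample.

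Two things are at stake. First, a reader cannot tell what the 95% power describes: which outcome, which comparison and what size of effect. Second, the article rests two claims of originality on the sample size, one for the overall effect and one for differences by income. The single figure of 95% is too low for the first and too high for the second if both are judged at 0.5.

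**Working it through.** **Inputs.** From Sample size: effect 0.5, alpha 0.05, power 0.95, enrolment 900 and 600, dropout 2/3 and 1/2, two income strata. From Statistical analyses: independent t-test. Assumptions: 0.5 is a standardised mean difference (d), the test is two-sided, and the income strata are equal in size.

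**Step 1: the dropout step reproduces.** 900 × (1 − 2/3) = 300 and 600 × (1 − 1/2) = 300. The plan therefore implies 300 completers per arm.

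**Step 2: the 300 does not reproduce.** The normal approximation is n per arm = 2(z₀.₉₇₅ + z₀.₉₅)² / d² = 2(1.960 + 1.645)² / 0.25 ≈ 104. The noncentral t gives 104.93, so 105. With the stated dropout:
- intervention: 105 / (1/3) = 315
- control: 105 / (1/2) = 210
- total: 525, against 1500 stated

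**Step 3: other readings of the inputs.**

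| Reading | Completers needed |
|---|---|
| One-sided t-test | 88 per arm |
| t-test, 1.5:1 allocation | 132 and 88 |
| Mann–Whitney, by assumed efficiency | 110 to 122 per arm |
| Paired t-test | 54 pairs |
| ANOVA, f = 0.5, 2 / 4 / 6 groups | 54 / 73 / 85 in total |
| Chi-square, w = 0.5, 1 to 3 df | 52 to 69 in total |
| Each income half powered separately | 2 × 105 = 210 per arm (630 + 420 = 1050 enrolled) |
| Arm-by-income interaction of 0.5 SD | 208 per cell, 416 per arm |

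The interaction row uses n per cell = 4(1.960 + 1.645)² / 0.25 ≈ 208. None of these gives 300 per arm. A near match appears only if alpha is cut to 0.05/6: 149 per group, or 298 per arm over two strata. The article does not state such an alpha, and it contradicts the 0.05 that it does state.

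**Step 4: what 300 completers per arm provide** (t-test, two-sided 0.05).

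| Comparison | Power at 0.5 | Detectable at 95% | Detectable at 80% |
|---|---|---|---|
| Overall, 300 v 300 | above 99.99% | 0.295 | 0.229 |
| Within an income half, 150 v 150 | 99.1% | 0.418 | 0.325 |

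For the arm-by-income interaction with 150 per cell, the standard error in SD units is √(4/150) = 0.163. Power for 0.5 SD is then Φ(0.5/0.163 − 1.960) ≈ 0.86. For a fixed 300 per arm, the sum of 1/n over the four cells is smallest when the cells are equal, so an uneven split would give less than 86%.

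**The case against.** The strongest reply is that nothing is put at risk. The article says that the arms were set at these sizes, not that the software returned 300. The income subdivision follows in the next sentence, so the authors may have enlarged the arms on purpose. At the stated effect, 95% power is exceeded overall and within each equal half. The article is also a condensed account, and the test, sidedness and software output may sit in a fuller document.

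Most of this stands. The gap is on the safe side for the effect stated, and the absence of the software output is not itself the point. What does not stand is the suggestion that the income split explains the numbers: it leads to 210 per arm for separate tests or 416 for an interaction, not 300.

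A reader might go further and infer that the trial is under-powered, because the Background cites a study in which "provision of information through bulletins board increased vegetable intake by 0.2 serving while a web-based intervention increased intake by 0.6 serving". That is a net 0.6 − 0.2 = 0.4 serving, or 28 g if a serving is 70 g. The document does not support this inference:
- It gives no SD. For assumed SDs of 100 to 180 g, power for 28 g with 300 per arm runs from about 93% to 48%, so the answer depends on the assumption.
- The 70 g serving is defined for this Japanese setting. The cited study is among those done outside Japan, and its serving size is not given.
- That study's comparison group received information, whereas here the controls wait. If controls do not change (assumption), 0.6 serving is 42 g, and power over the same SD range runs from above 99% down to 81%.
- The planned analysis is by intention to treat, and the calculation above counts completers only.
- Servings and grams are not units of either outcome in the Primary outcomes section.

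**Conclusion.** The stated basis for the sample size is wrong as written. The three inputs need 105 completers per arm under the test that the article names, against 300 implied, and no reading tried of those inputs closes the gap. The effect of 0.5 has no outcome attached, and the article names two different main outcomes, so the 95% cannot be assigned to anything.

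This is a faulty justification, not a shortage of participants. For d = 0.5, power is above 99.99% overall and about 99% in each income half. Only for a 0.5 SD difference in effect between income strata does it fall below the stated 95%, to about 86%. That bears on the secondary objective and on the income-strata claim in Strengths and limitations.

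The figures assume a standardised mean difference, two-sided testing at 0.05, the stated dropout, a comparison at a single time point, and (for the stratum and interaction figures) equal strata. The conclusion that 300 does not follow holds under every alternative listed above.

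**What to change.** Leave enrolment at 900 + 600 and restate what it provides. Suggested text for Sample size:

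> With 900 and 600 randomised and about 300 completers expected per arm, a two-sided t-test at the 0.05 level has 95% (80%) power for a standardised difference of 0.295 (0.229) in [named outcome]. If the income strata are of equal size (assumption), about 150 completers per arm in each stratum give 95% (80%) power for 0.418 (0.325). Power for a 0.5 SD difference in effect between the strata is about 86%.

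Fill in the outcome after settling which one is primary, since the Abstract and the Primary outcomes section differ. Confirm the test and sidedness, or recompute if another was used. If the low/high cut-off gives uneven strata, replace the 150 with the expected numbers. In Strengths and limitations, limit the claims of adequate size and of verifying differences by income to these effects.

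The cost is a few sentences and restated figures. No further participants are needed.
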